## Abstract

**Background:**

Zambia has one of the highest prevalence rates of HIV among adolescents and young adults (AYA) living with HIV in sub-Saharan Africa, which accounts for half of all new HIV cases as of 2023. Compared to their peers who are not living with HIV, AYA living with HIV are more likely to develop cancer. The most frequently diagnosed cancers among AYA living with HIV in Zambia are cervical cancer, Kaposi sarcoma, and non-Hodgkin lymphoma. Premature cancer mortality among AYA living with HIV is driven by late-stage presentation and poor treatment adherence.

**Objective:**

We aim to develop and test an integrated model of cancer control for AYA living with HIV that can be delivered as an embedded component in existing HIV treatment programs in primary care facilities and linked with specialized treatment at cancer centers.

**Methods:**

We propose a cluster randomized controlled trial to compare the AYAHIV Role-Based Responsibilities for Oncology-Focused Workforce (ARROW) program with a one-time education campaign. The ARROW program consists of interventions at the individual, health care provider, and health system levels. Peer counselors will educate AYA living with HIV through one-on-one and group education sessions and offer care coordination and linkages with clinicians. The HIV and oncology workforce will receive collaborative education and training. The ARROW Health Care Collaborative will connect administrators and policy makers to address system-level barriers. The study will recruit AYA living with HIV between the ages of 15 and 39 years who have been on antiretroviral therapy for at least 6 months and are not pregnant; the cancer treatment cohort will enroll AYA living with HIV who have been diagnosed with cervical cancer, Kaposi sarcoma, or non-Hodgkin lymphoma in Lusaka, Zambia. Half of the 18 HIV facilities have been randomly assigned to a one-time educational campaign and the other half to the ARROW intervention. Participants in the cancer treatment cohort will be randomized into 1 of the 2 study arms. We will conduct economic evaluations to assess the cost-effectiveness of the ARROW program. We will use an intent-to-treat approach to test the hypothesis that AYA living with HIV in the ARROW program will have higher uptake of diagnostic services, increased adherence to treatment, and improved outcomes compared to those receiving one-time education.

**Results:**

As of March 2025, early detection cohort recruitment concluded with 3442 participants and cancer treatment cohort enrollment is ongoing, with 105 participants thus far. Results pertaining to the 12-month end points will be available in early 2026.

**Conclusions:**

If successful, the ARROW program will offer a model to improve cancer prevention, early diagnosis, and treatment through improved integration between HIV and cancer services. Furthermore, ARROW can provide a framework for implementing expanded services, such as survivorship care, for AYA living with HIV.

**International Registered Report Identifier (IRRID):**

DERR1-10.2196/68254

## Introduction

### Background

Adolescents and young adults (AYA), those aged 15 to 39 years, represent a growing share of people living with HIV worldwide. Zambia has one of the highest prevalence rates of HIV among AYA in sub-Saharan Africa; as of 2023, there are approximately 90,000 AYA between the ages of 10 and 19 years living with HIV, with only half of that population receiving antiretroviral therapy (ART) [1]. The AYA population also accounts for half of all new recorded infections in the country [1]. Compared to their peers who are living without HIV, AYA living with HIV are at an increased risk of developing cancer [2-4]. Cancers most frequently diagnosed among AYA living with HIV in Zambia are Kaposi sarcoma (KS), non-Hodgkin lymphoma (NHL), and cervical cancer (CC) [5-9]. The incidence of these cancers increases with a lower cluster of differentiation 4 cell count (CD4); therefore, adherence to ART is paramount [10]. Unfortunately, AYA living with HIV are among the most vulnerable groups with poor adherence to ART, and there is no large-scale cancer control program to facilitate early diagnosis and completion of guideline-recommended treatments in Zambia [11,12].

A cancer program focused on AYA living with HIV and tailored to the Zambian limited resource setting is needed to reduce premature mortality. Data on malignancies within this group are sparse, but late-stage presentation, unplanned breaks from cancer treatment, and abandonment of treatment have been reported among young patients with cancer in resource-limited settings [13-15]. These factors result in high morbidity and premature mortality among AYA living with HIV and diagnosed with cancer. Late-stage presentation and lack of treatment adherence are key drivers of premature cancer mortality among AYA living with HIV in Zambia.

AYA living with HIV are a vulnerable population who face psychosocial issues, stigma, and comorbidities that affect their health care-seeking behavior [16]. In Zambia, young patients living with both HIV and cancer have unmet needs related to information about health risks, coping strategies for medication side effects, positive peer and family support, and activation of personal agency [17-20]. Furthermore, during the transition from pediatric to adult HIV clinics, many of these individuals are lost to care [21-25]. Health care providers who specialize in HIV care and oncology face barriers, such as time constraints, with regard to treating cancer in AYA living with HIV, which inhibits their ability to deliver optimal care [26,27]. There are also no linkages for collaborative management of cancer in AYA living with HIV by primary care providers specializing in HIV care and cancer specialists. At the health system level, some key barriers include weak referral systems and a lack of standardized protocols to implement AYA-friendly care [28-32].

The Zambian guidelines recommend CC screening for all female AYA living with HIV who are sexually active, regardless of age [33]. However, screening among this population is low, despite the availability of free health care services. According to recent studies [18,34], <40% of AYA living with HIV have undergone screening for CC. There are no screening tests available for KS or NHL, but increasing awareness of the risk factors and symptoms, along with physical examinations, could reduce late presentation [13,29]. In fact, strategies to facilitate early detection of KS have shown promise in other African countries. A recent study in Uganda [35] used education messaging (comic strip and video) to increase KS awareness and knowledge. Furthermore, researchers in Zimbabwe developed a physical examination checklist to identify symptoms of KS [36]. The Cancer Diseases Hospital, which is the main referral center for treatments in Zambia, has adopted the National Comprehensive Cancer Network’s (NCCN’s) Harmonized Guidelines for sub-Saharan Africa for AYA oncology to optimize treatment. The NCCN guidelines will be most effective when paired in tandem with adequate treatment adherence support for AYA living with HIV.

AYA-focused programs have been successful in other settings, especially in high-income countries. These programs use a variety of models to promote collaboration across multidisciplinary teams and integrate medical and psychosocial care for AYA [37-39]. In sub-Saharan African countries such as Zambia, multiple barriers need to be addressed to facilitate early diagnosis in the primary care setting and to ensure receipt of full treatment course in cancer centers [40].

### Objective

We aim to develop and test an integrated model of cancer control for AYA living with HIV that can be delivered as an embedded component in existing HIV treatment programs in primary care facilities and linked with specialized treatment in cancer centers.

## Methods

### Overview and Conceptual Framework

#### Overall Approach

We propose a program that embeds cancer control strategies for AYA living with HIV into existing HIV treatment programs in primary care facilities and at cancer centers in Zambia by strengthening and supporting the existing clinical teams to optimize cancer care delivery. We used theory-informed multilevel strategies to create the AYAHIV Role-Based Responsibilities for Oncology-Focused Workforce (ARROW) program to increase uptake of services for early diagnosis and improve compliance with cancer treatment for CC, KS, and NHL. ARROW will use an evidence-driven approach to select low-cost, multilevel peer-to-peer support and learning strategies to address identified barriers and delineate roles played by HIV and cancer care providers to deliver guideline-directed care for early diagnosis and cancer treatment. Each of the proposed strategies has been tested in the Zambian and sub-Saharan African context and shown to be feasible [18,41-45].

Our overall approach is based on the evidence-based strategy of peer support for engagement and learning [46-54]. Figure 1 presents the theoretical framework, which is based on the socioecological model [55]. We have created the ARROW program with strategies that focus on barriers at the individual, health care provider, and health system levels. These strategies are guided by the capability, opportunity, motivation, and behavior model, in which capability (eg, knowledge and cancer risk), opportunity (eg, availability of high-quality screening and treatments), and motivation (eg, self-efficacy and care-seeking behavior) interact to facilitate behavior change [55].

**Figure 1 figure1:**
[figure not shown]
Conceptual framework for addressing barriers to reduce cancer mortality. ARROW: AYAHIV Role-Based Responsibilities for Oncology-Focused Workforce; ART: antiretroviral therapy; AYA: adolescents and young adults.

#### Interventions

The ARROW program is a holistic intervention that is meant to support HIV and cancer care at 3 different levels: individual, health care provider, and health system.

#### Individual Level

There is growing evidence on the role that peer support can play in addressing individual and interpersonal barriers to improve knowledge and encourage AYA to seek medical care [56-62]. We will place trained peer counselors (PCs) in HIV treatment facilities and at the Cancer Diseases Hospital to educate AYA living with HIV, provide emotional support, and offer care coordination and linkages with the clinical team. PCs will offer support for early diagnosis of cancers, completion of cancer treatment, and ART adherence as required. They will coordinate care with health care providers and serve as an extension of the clinical team by conducting physical examinations to identify signs of KS and NHL and offering coping strategies for ART and chemotherapy side effects.

A total of 21 PCs, 10 (48%) males and 11 (52%) females between the ages of 20 and 39 years, will be recruited. Of the 21 PCs, 18 (86%; 9/18, 50% males and 9/18, 50% females) will receive traning for placement in HIV treatment centers. The remaining 3 PCs (14%; 1/3, 33% male and 2/3, 67% females) will be posted to the Cancer Diseases Hospital. The recruitment of more female PCs is due to the heavy burden that CC places on the health care system. Our existing 3-week training curriculum, from a previous study [18] conducted by the research team, will be tailored for PCs and will include training on appointment tracking systems. The curriculum will include standardized operating procedures for implementing the group education sessions to include additional details on cancer risk, early diagnosis approaches, and optimal treatments. Those assigned to the Cancer Diseases Hospital will receive training on how to help AYA living with HIV manage treatment side effects and assist with their adherence to ART while undergoing cancer treatment. The PCs will conduct site visits of the HIV facilities and the Cancer Diseases Hospital to become familiar with the staff, the layout of the clinics, and the services available.

Table 1 summarizes the 4 core PC roles and their corresponding activities. The PCs will offer 6 group education sessions at each ARROW HIV facility per month (one module each month) for the first 12 months, along with one-on-one education. For the remaining follow-up period, PCs will offer one-on-one education as needed. All other activities will continue throughout the trial.

**Table 1 table1:** Key functions of peer counselors (PCs).

Functions	HIV treatment facility	Cancer diseases hospital
HIV and cancer knowledge	Group and one-on-one education on cancer early diagnosis and ART^a^ adherence	One-on-one education on cancer treatment and ART adherence; some group sessions
Social and emotional support	Group sessions and individual meetings to discuss coping with stigma, family stressors, and side effects (ART or cancer treatment)	Group sessions and individual meetings to discuss coping with stigma, family stressors, and side effects (ART or cancer treatment)
Care-seeking behavior	Motivational interviews; PCs offer convenient times for physical examinations; reminder phone calls before visits	Documenting treatment plan; tracking of visits to remind AYA^b^ living HIV about visits; identifying and addressing barriers
Care coordination	Accompany AYA living with HIV to referral visits; facilitate delivery of results to the HIV care team; inform AYA living HIV about the next steps	Ensure that the cancer care team is aware of any barriers to adherence; facilitate communication with the HIV care team

^a^ART: antiretroviral therapy.

^b^AYA: adolescents and young adults.

Educational materials will be made for the 2 study arms of the randomized controlled trial by adapting existing group and one-on-one educational materials, such as training modules previously tested for KS awareness or the NCCN AYA Guidelines for Patients. These materials will be presented at pretesting workshops. Trained facilitators will present materials to ensure that they are age-appropriate by assessing participants’ ability to understand, whether the topics and contents address key issues faced by the age group, and whether AYA living with HIV can embrace and follow the solutions or advice offered. Using the feedback received, we will finalize the modules and brochure. All adapted education materials for AYA living with HIV will be available in English, Bemba, Nyanja, and Tonga. Health care provider guidance documents will be available in English, as in previous projects; all Zambian health care providers are fluent in English.

A treatment plan based on the NCCN treatment and survivorship plans will be developed for study participants at the Cancer Diseases Hospital. The PCs will update treatment plans for AYA living with HIV through the treatment course, which will serve as a comprehensive record that can also be placed in the patient file at the HIV treatment center that the AYA living with HIV will return to after treatment completion.

#### Health Care Provider Level

Team-based care is critical for optimal oncology care delivery [61,62]. Formalized communication channels, collective learning, and clear team roles are the cornerstone of collaborative care teams [63,64]. The ARROW Provider Network will use a tailored Project Extension for Community Healthcare Outcomes approach to link pediatric and adult health care providers who specialize in HIV care in the primary care facilities with counterparts at the Cancer Diseases Hospital to enable peer-to-peer learning, review of patient cases, and expert consultations [44].

Guidance documents and brochures will be created for health care providers by inviting a mix of pediatric and adult care providers to cocreating workshops. These materials will contain background information, AYA-friendly care delivery, age-appropriate engagement with AYA living with HIV, monitoring of ART adherence, flowcharts with referral pathways for early diagnosis, process steps to implement guideline-recommended cancer treatment for AYA living with HIV, documentation of services provided (eg, in the SmartCare electronic health record, which is used in HIV facilities and capture visit details, medications, and laboratory tests), and a charter with roles and responsibilities for clinical teams in the HIV treatment centers and those at the Cancer Diseases Hospital. Facilitators will use the NCCN sub-Saharan African harmonized guidelines for each cancer, along with the AYA guidelines, and create guidance documents focused on AYA living with HIV that are tailored to the Zambian setting.

Health care providers will also receive in-person training at each of the 9 HIV facilities selected to implement the ARROW program and at the Cancer Diseases Hospital before initiating the implementation trial. These training programs will also include sessions on understanding stigma faced by AYA living with HIV, delivering age-appropriate and AYA-friendly care, and best practices for communication with this population using previous training tools [17]. All HIV care providers (both pediatric and adult) will be encouraged to attend a session. We will hold additional training as needed, including refresher training sessions during the 36-month trial.

We will initiate activities to facilitate collaborative learning and coordination by hosting (1) monthly peer-to-peer web-based sessions with presentations from Zambian and international physicians working to improve AYA cancer care, case reviews for AYA living with HIV, and expert consultation panels to address specific questions from the ARROW Provider Network; (2) an annual in-person meeting in Lusaka to review progress and next steps; and (3) an in-facility biannual seminar with adult and pediatric teams on specific issues related to AYA living with HIV.

#### Health System Level

We will initiate the ARROW Health Care Collaborative, which will bring together health system administrators and Zambian Ministry of Health policy makers to foster team-based problem solving and implementation of solutions to address system-level barriers (eg, barriers related to referrals). We will also use a user-centered design process to cocreate education materials and guidance documents to implement ARROW.

We will invite 6 health care administrators from Lusaka province and 4 Ministry of Health policy makers to join the Collaborative to foster team-based problem solving. These individuals will meet quarterly to review implementation challenges related to referral pathways and other system-level barriers to receiving services to facilitate early diagnosis and optimal cancer treatment. Each meeting will end with clear action steps toward resolving the barriers and procedures that will be used to monitor the implementation of the proposed solutions. The first meeting of the Collaborative will take place 6 months before the start of the trials to allow adequate time to identify and address any gaps identified through the readiness assessment. The reduction in barriers will benefit not only the ARROW program participants but also all AYA living HIV in Lusaka province.

### Randomized Controlled Trials

#### Overall Study Design

##### Overview

We will compare the ARROW program to a one-time education campaign that gives informational brochures to AYA living with HIV and HIV care providers. Given the acute need for cancer control strategies for AYA living with HIV to reduce premature mortality, planning consultations with community stakeholders deemed it unethical to use “usual care” as the comparison arm. We will, therefore, test the hypothesis that the ARROW program will be more effective than a one-time education campaign (education brochures to AYA living with HIV and HIV providers) in increasing care received by AYA living with HIV to facilitate early diagnosis (physical examination for KS and NHL, CC screening, and timely referrals) and in improving adherence to treatment among AYA living with HIV diagnosed with cancer. We will also assess implementation outcomes (based on the Proctor framework), analyze determinants of implementation (based on the Consolidated Framework for Implementation Research), and conduct economic evaluation of the ARROW program [65,66].

##### Early Detection Cohort

We propose a cluster randomized study to be implemented at 18 HIV treatment facilities in Lusaka province. Three facilities serving each type of regional population (urban, periurban, or rural populations) will be randomly assigned to a study arm: the ARROW program or one-time education. Overall, 9 (50%) facilities will be assigned to each arm of the trial, with data collection at baseline and at 12-, 24-, and 36-month follow-up. At each of the 18 clinics, we will enroll 100 men and 100 females resulting in a total of 3600 participants in the early detection cohort. The 200 AYA living with HIV per facility will be selected by first reviewing the HIV register and identifying those who meet the study inclusion criteria: 15 to 39 years of age, on ART for at least 6 months, not pregnant, and with no pending plans to move from the current residence during the 3-year study duration. For all the 3600 participants, we will collect baseline data and capture information on study end points from the SmartCare system, and the supplemental data will be collected by PCs and trained study data collectors (eg, tracking referrals for all participants and obtaining results of biopsies).

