##### Cancer Treatment Cohort

This will take place entirely at the Cancer Diseases Hospital, with some patients being recruited from the University Teaching Hospital. A total of 500 AYA living with HIV who have been diagnosed with CC, NHL, or KS will be recruited into the study, with 50% (250/500) of the patients in each trial arm (ie, one-time educational campaign vs the ARROW intervention). Patients will be surveyed annually at 12, 24, and 36 months. Trained data collectors will obtain consent and enroll AYA living with HIV, aged 15 to 39 years. We will be aiming for the following targets for each cancer type: 50% (250/500) of the participants with CC, 30% (150/500) of the participants with KS, and 20% (100/500) participants with NHL (with an overall equal number of male and female AYA living with HIV for KS and NHL). While AYA living with HIV who are pregnant will be excluded, as they require specialized care, those who become pregnant during the trial period will remain enrolled in the study; CC screening and physical examinations for KS and NHL will be offered based on Zambian guidelines pertaining to pregnancy.

We hypothesize that, by facilitating peer support to address barriers and gaps at multiple levels, the ARROW program will be more effective than the one-time education campaign, but more expensive as well. As shown in Figure 2, we will simultaneously conduct separate randomized controlled trials at the HIV treatment facilities and at the Cancer Diseases Hospital. The trials will be initiated upon completion of the preimplementation preparation activities. We will then embed PCs into the care teams at the HIV facilities and the Cancer Diseases Hospital and initiate the planned implementation activities of the ARROW Provider Network in the ARROW program arm. The comparison arm will receive the one-time education campaign: health care providers at the HIV facilities (particularly physicians and nurses) will receive a brochure with key guidance for early diagnosis of cancers in AYA living with HIV, and the AYA living with HIV upon recruitment will also receive education brochures at both the HIV facilities and the Cancer Diseases Hospital. The Health Care Collaborative will continue to meet as planned on a quarterly basis.

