#### Study End Points

##### Early Detection Cohort

We will assess effectiveness based on dual primary end points. The first primary end point is the proportion of those who complete a physical examination visit for KS and NHL and the proportion of those who are up to date with CC screening (female participants only) at 12 months. The second primary end point is the proportion of those who complete the recommended follow-up supplemental or diagnostic procedures (within 3 months of receiving follow-up referral), those who initiate cancer treatment (within 3 months of diagnosis), and those who complete additional cancer detection visits over 36 months. The secondary end point, evaluated at 36 months, is the proportion of those diagnosed at an early stage (among those diagnosed with KS, NHL, and CC). We will likely have a few cancer cases in the study facilities. Therefore, these findings will not be conclusive but will offer insights into the potential impact of the ARROW program on facilitating diagnosis at an early stage.

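### First primary end point: recording of examinations and screening can be more complete under ARROW than under control, and no arm-neutral check is described

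*Protocol article*

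**What the plan says.** All references are to the protocol article.

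**End point and its sources.** Under Study End Points, the first primary end point is "the proportion of those who complete a physical examination visit for KS and NHL", together with being up to date with CC screening (female participants), at 12 months. Under Overall Study Design, Early Detection Cohort, the study will "capture information on study end points from the SmartCare system" for all participants. The same sentence adds that "the supplemental data will be collected by PCs and trained study data collectors (eg, tracking referrals for all participants and obtaining results of biopsies"). Table 2 names clinical records and the PC tracking tool as the confmation of these services, with the study database as a further source.

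**What ARROW providers receive.** The Health Care Provider Level section describes guidance documents and brochures for providers, whose contents include "documentation of services provided (eg, in the SmartCare electronic health record"). It then states: "Health care providers will also receive in-person training at each of the 9 HIV facilities selected to implement the ARROW program". Refresher sessions, monthly web-based Network sessions and in-facility seminars follow. The study will embed PCs and "initiate the planned implementation activities of the ARROW Provider Network in the ARROW program arm". The Individual Level section gives PCs the task of "conducting physical examinations to identify signs of KS and NHL".

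**What control providers receive.** Physicians and nurses at the control HIV facilities "will receive a brochure with key guidance for early diagnosis of cancers in AYA living with HIV".

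**The concern.** An examination with a negative finding need not lead to a referral, a biopsy or a laboratory result. If nobody writes it down, it counts as not done. The end point therefore measures the product of two things: whether the service happened, and whether it was recorded. ARROW is meant to change the first, but its provider component and its PCs can also change the second. The PC tracking tool gives ARROW participants an additional route to a counted event, since PCs work in the ARROW arm and perform some of the examinations themselves.

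If recording is more complete under ARROW, the estimated gain in uptake is too large, and so is the gain used in the cost per person receiving early detection services. A larger sample does not remove this bias. Without data on completeness by arm, no model fitted later can separate uptake from recording.

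**Working it through.** **Inputs from the article** (Sample Size and Recruitment; Overall Study Design): 9 facilities per arm; 200 participants per facility, 100 of them female; 10% attrition, so m = 180 for examination and m = 90 for screening; ICC 0.03 to 0.05; two-sided alpha .025; control uptake 15% (examination) and 20% (screening); success threshold 20 points.

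**Step 1: the plan's own power.** Design effect = 1 + (m − 1) × ICC, and effective n per arm = 9m / design effect. SE = √[(p0q0 + p1q1) / effective n]. Power comes from the noncentral t with 16 df (critical value 2.473).
- Examination, 15% v 35%. ICC 0.05: design effect 9.95, effective n 163, power 95.5%. ICC 0.03: design effect 6.37, effective n 254, power 99.6%. The article states over 90%.
- Screening, 20% v 40%. ICC 0.05: design effect 5.45, effective n 149, power 90.4%. ICC 0.03: design effect 3.67, effective n 221, power 98.1%. The article states over 85%.

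The stated power is met, so the issue is bias, not sample size.

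**Step 2: a recording gap with no true effect.** Recorded uptake = true uptake × share recorded, with the same true uptake in both arms. The article gives no recording shares, so those below are assumptions. Recorded control uptake is held at the article's 15%, and ARROW is assumed to record 90%. The last column is the chance that the test at two-sided .025 favours ARROW; its nominal value is .025 / 2 = 1.25%.

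| Control share recorded | True uptake, both arms | Recorded, control v ARROW | Spurious gain | Chance of significance for ARROW (ICC .05 to .03) |
|---|---|---|---|---|
| 75% | 20% | 15% v 18% | 3 points | 5.9% to 8.1% |
| 60% | 25% | 15% v 22.5% | 7.5 points | 26% to 41% |
| 50% | 30% | 15% v 27% | 12 points | 59% to 80% |

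First row in full, ICC 0.03: SE = √[(.15 × .85 + .18 × .82) / 254.3] = 0.0329; noncentrality = 0.03 / 0.0329 = 0.91; tail probability 8.1%. At ICC 0.05: SE = 0.0411, noncentrality 0.73, tail probability 5.9%.

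For screening, with recorded control uptake at 20%, the 60% v 90% gap gives 20% v 30%: 10 points, and a 35% to 50% chance.

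**Step 3: what recording alone needs to reach 20 points.** The ratio of control to ARROW completeness would have to be .15 / .35 = 0.43 for examination, or .20 / .40 = 0.50 for screening.

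**Step 4: a smaller gap on top of a real effect.** Suppose screening truly rises by 10 points, from 33.3% to 43.3%, with 60% recorded in control and 95% under ARROW (assumed). Recorded uptake is .333 × .60 = 20.0% v .433 × .95 = 41.2%, an apparent gain of 21.2 points.

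**The case against.** Several stronger readings are tempting, and the article does not support them.

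- **That SmartCare is the only source.** It is not. Study data collectors supplement it, Table 2 adds the PC tool and the study database, and paper files are abstracted in some settings. This stands. However, the examples given for supplemental collection are referrals and biopsy results, which come after the examination, and the PC tool adds to the asymmetry.
- **That only ARROW providers are told to document in SmartCare.** The documentation content is listed for guidance documents and brochures together, so the control brochure may carry some of it. The training topics that the article names are stigma, age-appropriate care and communication, not record entry. What is established is a difference in intensity of contact and in the presence of PCs, not record training in one arm only.
- **That the plan has no participant report of these services.** Table 2 lists a self-reported cancer survey at baseline and at 12, 24 and 36 months. Its items are not shown and may include screening history. One can say only that no arm-neutral check is described.
- **That recording could by itself make ARROW a success.** None of the scenarios in the table reaches the plan's 20-point threshold as an expected gain. Even with a 12-point spurious gain, the chance of an estimate of 20 points or more is about 1% to 4% (normal approximation, same SE formula).

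The recording shares are also assumptions, and the two larger gaps may be thought extreme. That is fair. It limits what can be said about size, not the mechanism.

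**Conclusion.** The concern holds as a risk of differential ascertainment in ARROW's favour on the first primary end point. It rests on three features of the article: the end point comes from facility records and a PC tool; provider training, Network sessions and PCs belong to ARROW; and the Limitations section covers baseline imbalance, missing data and provider turnover, but not differential recording. The described quality control monitors data collectors' fidelity to the protocol. It is not described as looking for services that were delivered but not recorded.

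The size cannot be known from the document. Under the modest assumed gap (75% v 90%) the distortion is about 3 points and the false-positive chance 6% to 8% instead of 1.25%. Larger gaps give more. The threshold of 20 points is protected against recording alone unless control completeness is about half of ARROW's or less, but a smaller gap could lift a real effect that falls short of 20 points over it. This should be corrected, but it does not invalidate the design.

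**What to change.** 1. Define the first primary end point from one set of sources available in both arms (SmartCare, paper files, screening site registers), abstracted in the same way by the existing data collectors.
2. Add a sensitivity analysis that excludes events found only in the PC tracking tool.
3. If the 12-month survey does not already ask, add items in both arms on whether, when and where the participant had a KS/NHL examination and, for women, CC screening. Report by arm the share of self-reported services found in the records. If the 12-month wave has passed, do this at 24 months.
4. Use that share only in a sensitivity analysis. Self-report is not an arm-neutral standard: ARROW participants are repeatedly educated and reminded about these services, so their reporting may itself differ from that of controls.

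Do not give control facilities a new instruction on record entry. Recruitment has closed and ARROW has been launched, so that would change the comparator in a running trial.

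The cost is a few survey items and some extra abstraction by staff already employed.
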